### Trial site responsibilities

Participants will be advised to record the nature, timing and duration of any AEs with clear guidance on when to stop the medication and when and how to report back to the named clinician at the participating mental health facilities. These clinicians will have received the basic training required in this regard. All non-serious AEs and ARs, whether expected or not, should be recorded in the participant’s medical notes and recorded in the study AE Form by the researcher and sent to the country trial manager/ coordinator within an agreed timescale (preferably three days)- the details will be provided in the ‘Adverse Event and Serious Adverse Event Reporting’ standard operating procedure (SOP). SAEs and SARs should be notified to the country lead (a medical doctor) within 24 hours of the researcher/clinical team becoming aware of the event.

#### Trial site assessment

Seriousness

When an AE or AR occurs, the clinical team responsible for care of the participant must first assess whether or not the event is serious using the definition given in Table 2. If the event is serious, then an SAE/SUSAR Form must be completed and the country lead or trial manager notified within 24 hours.

Severity or Grading of Adverse Events

This relates to the intensity or severity of the event experienced by the participant. The severity of all AEs and/or ARs (serious and non-serious) in this trial should be based on the clinical team’s (supported by the country lead or trial manager if needed) judgement using the following definitions:

- Mild: An event that is easily tolerated by the participant, causing minimal discomfort and not interfering with everyday activities.
- Moderate: An event that is sufficiently discomforting to interfere with normal everyday activities.
- Severe: An event that prevents normal everyday activities.

*NOTE: Severity should not be confused with the seriousness of the event which relates to the participant or event outcome.*

Causality

The country leads or mental health care team must assess the causality of all serious events or reactions in relation to the trial therapy using the definitions in Table 3. Alternative causes, such as natural history of the underlying diseases, concomitant therapy, other risk factors etc. should be considered. There are five categories: unrelated, unlikely, possible, probable, and definitely related. If the causality assessment is unrelated or unlikely to be related, the event is classified as an SAE. If the causality is assessed as possible, probable or definitely related, then the event is classified as an SAR.

**Table 3: Assigning Type of SAE through Causality**

| **Relationship** | **Description** | **SAE type** |
| --- | --- | --- |
| Unrelated | There is no evidence of any causal relationship | Unrelated SAE |
| Unlikely | There is little evidence to suggest that there is a causal relationship (for example, the event did not occur within a reasonable time after administration of the trial medication). There is another reasonable explanation for the event (for example, the participant’s clinical condition, other concomitant treatment). | Unrelated SAE |
| Possible | There is some evidence to suggest a causal relationship (for example, because the event occurs within a reasonable time after administration of the trial medication). However, the influence of other factors may have contributed to the event (for example, the participant’s clinical condition, other concomitant treatments). | SAR |
| Probable | There is evidence to suggest a causal relationship and the influence of other factors is unlikely. | SAR |
| Definitely | There is clear evidence to suggest a causal relationship and other possible contributing factors can be ruled out. | SAR |

Expectedness

If there is at least a possible involvement of the trial treatment, the country lead or mental health care team must assess the expectedness of the event. An unexpected adverse reaction is one not previously reported in the current Summary of Product Characteristics or one that is more frequent or more severe than previously reported. The definition of an unexpected adverse reaction (UAR) is given in Table 2. The ‘Adverse Event and Serious Adverse Event Reporting’ SOP will contain a list of expected toxicities associated with the medications being used in this trial. If a SAR is assessed as being unexpected, it becomes a SUSAR.

Notification

The country lead or trial manager should be notified of all SAEs **within 24 hours** of the site’s mental health care team or researcher becoming aware of the event. The mental health care team should notify country lead or trial manager of all SAEs occurring from the time of randomisation until 30 days after the last protocol treatment administration using the SAE/SUSAR Form. SARs and SUSARs must be notified to the country trial managers or country leads until trial closure.

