### Details of the interventions

#### Arm 1: Brief advice

Participants randomised to trial arm 1 will receive brief advice (BA) adapted from a community-based trial of tobacco cessation in India.^39^ As part of BA, participants will receive verbal information on the harmful effects of tobacco and will be advised to stop smoking. BA will be delivered by trained psychology graduates in Pakistan and psychology graduates and social workers in India on the same day as enrolment and will last up to five minutes. This will be a one-time interaction: participants in this trial arm will not have any further BA sessions with the psychology graduates and social workers. Participants will be provided with an information leaflet containing the same advice in a written format to take home.

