### Baseline and follow-up data collection

Data will be measured and collected from participants and carers face-to-face or remotely at baseline, one, three and six months. Data will be either be entered in paper format or directly into an online survey tool (Qualtrics)^46^ using tablets.

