### Adverse event monitoring

AEs will be assessed at each counselling session and at the face-to-face follow-up visits, and their potential association with study interventions or procedures ascertained. The researcher conducting the counselling session or follow-up visit assessments will record all directly observed AEs and all AEs reported by the study participant. An adverse events review checklist will be developed to be used at each visit / session to explicitly prompt for symptoms relating to possible nicotine replacement therapy or bupropion related toxicities. This way we will be able to address any AEs or concerns that the participants might have.

In the context of this study, it is very unlikely that any AEs would be related to the behavioural support within the IMPACT 4S intervention nor the BA as they are educational and motivational intervention and that are not harmful. The research procedures are also very low risk. Nevertheless, there is a potential for AEs due to the pharmacotherapies (nicotine replacement therapy or bupropion). AEs will be reported on the AE form. Serious adverse events will be defined according to ICH GCP, and will be reported to the respective country coordinating centres according to the agreed timelines.

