**Table 2. AE definitions**

| **Term** | **Definition** |
| --- | --- |
| Adverse Event (AE) | Any untoward medical occurrence in a participant to whom an IMP has been administered including occurrences that are not necessarily caused by or related to that product. |
| Adverse Reaction (AR) | Any untoward and unintended response to an IMP related to any dose administered. |
| Unexpected Adverse Reaction (UAR) | An adverse reaction, the nature or severity of which is not consistent with the information about the medicinal product in question set out in the SPC for that product, participant information leaflet, IB or protocol. |
| Serious Adverse Event (SAE) or Serious Adverse Reaction (SAR) or Suspected Unexpected Serious Adverse Reaction (SUSAR) ^***^ | Respectively any adverse event, adverse reaction or unexpected adverse reaction that:   - Results in death - Is life-threatening^*^ - Requires hospitalisation or prolongation of existing hospitalisation^**^ - Results in persistent or significant disability or incapacity - Consists of a congenital anomaly or birth defect |

^*^The term life-threatening in the definition of a serious event refers to an event in which the participant is at risk of death at the time of the event; it does not refer to an event that hypothetically might cause death if it were more severe, for example, a silent myocardial infarction.

^**^Hospitalisation is defined as an inpatient admission, regardless of length of stay, even if the hospitalisation is a precautionary measure for continued observation. Hospitalisations for a pre-existing condition, that has not worsened or for an elective procedure do not constitute an SAE.

^***^ Medical judgement should be exercised in deciding whether an AE or AR is serious in other situations. The following should also be considered serious: important AEs or ARs that are not immediately life-threatening or do not result in death or hospitalisation but may jeopardise the participant or may require intervention to prevent one or the other outcomes listed in the definition above.

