### Country PI/ lead responsibilities

Medically-qualified staff at the country coordinating centre (the country trial manger or lead) will review all SAE reports received. The events will be coded using the Medical Dictionary for Regulatory Activities ([MedDRA](http://www.meddra.org/)). The causality assessment given by the mental health care team at the mental health facility cannot be overruled; in the case of disagreement, both opinions will be provided in any subsequent reports.

The country leads are responsible for reporting the SAEs to the competent authorities (drug regulatory authorities and REC/IRB) in their respective countries and to the University of York research team in the UK. Fatal and life-threatening SUSARs must be reported to the competent authorities (drug regulatory authorities and REC/IRB) within 7 days of the country coordinating centre being notified of the event and follow-up information within a further 8 days; other SUSARs must be reported within 15 days.

The University of York research team should be notified of all SAEs **within 24 hours** of the site mental health care team’s becoming aware of the event. The country leads should notify the University of York research team of all SAEs occurring from the time of randomisation until 30 days after the last protocol treatment administration using the SAE/SUSAR Form. SARs and SUSARs must be notified to the University of York research team until trial closure.

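### SAE notification ends 30 days after last treatment and an AE requires an IMP, so crude SAE and AE counts are not comparable between arms

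*Protocol*

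**What the plan says.** **SAE window.** The Notification paragraph of section 10.4 covers "all SAEs occurring from the time of randomisation until 30 days after the last protocol treatment administration using the SAE/SUSAR Form". Section 10.6 sets the same limits for onward reporting to the University of York. SARs and SUSARs are notified until trial closure. The opening of section 10.4 and its Seriousness paragraph require serious events to be notified within 24 hours of awareness and give no end date.

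**Treatment length.** In section 5.1, brief advice is given "on the same day as enrolment and will last up to five minutes". It is not repeated: "This will be a one-time interaction: participants in this trial arm will not have any further BA sessions". Arm 2 has up to 15 sessions over three to four months (Summary) and is offered about three months of medication (section 5.1).

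**Definition.** Table 2 defines an AE as "Any untoward medical occurrence in a participant to whom an IMP has been administered", and its SAE definition builds on that.

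**Assessment.** Section 10.2 states that "AEs will be assessed at each counselling session and at the face-to-face follow-up visits". The same section provides a checklist for every visit or session. Section 5.16 gives both arms follow-up at one, three and six months, and section 5.15 allows it to be remote: "Data will be measured and collected from participants and carers face-to-face or remotely at baseline, one, three and six months".

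**The concern.** The period in which an SAE must be notified is set by how long a participant is treated, and treatment length is what differs between the arms. Take an admission on day 60 that is judged unrelated to treatment. Under the Notification paragraph it falls outside the window in Arm 1 and inside it for an Arm 2 participant still in treatment. The arms can then show different SAE counts when the true risk is the same.

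The IMP-based definition is a second, separate problem. Arm 1 receives no IMP, and Arm 2 participants may decline the drugs, so read literally neither group can have an AE or SAE. The rest of the protocol does not work that way. Section 10.1 treats research procedures and behavioural support as possible sources of AEs, section 10.2 asks about association with study interventions or procedures, and section 10.4 starts notification at randomisation.

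What is at stake is descriptive reporting and oversight. AE reports can lead to the trial being stopped (section 10.8), and the DMEC can recommend closing recruitment to an arm (section 12.3). An analysis can allow for unequal person-time, but it cannot recover events that were never notified.

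**Working it through.** The protocol states no total window per arm, so there is no figure of its own to reproduce. The windows follow from its rules.

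**Inputs from the protocol**
- Window: randomisation to last treatment + 30 days (sections 10.4 and 10.6).
- Last treatment in Arm 1: day 0 (section 5.1).
- Last treatment in Arm 2: month 3 to month 4 (Summary and section 5.1).
- Follow-up: 6 months in both arms (section 5.16).
- Size: 172 at 1:1 (sections 5 and 5.18), so 172 / 2 = 86 per arm.

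**Assumptions not in the protocol**
- A six-month SAE risk of 5%, 10% or 20%, equal in both arms, at a constant hazard.
- The AE definition is applied to all randomised participants, Arm 2 treatment is completed, and there is no attrition.

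**Windows**, with 1 month = 365.25 / 12 = 30.44 days and follow-up = 182.6 days
- Arm 1: 0 + 30 = 30 days, or 30 / 182.6 = 16% of follow-up.
- Arm 2, three months: 3 × 30.44 + 30 = 121.3 days (66%).
- Arm 2, four months: 4 × 30.44 + 30 = 151.8 days (83%).
- Ratio: 121.3 / 30 = 4.0 to 151.8 / 30 = 5.1.
- Person-years: 86 × 30 / 365.25 = 7.1 in Arm 1, against 28.6 to 35.7 in Arm 2.

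**Expected participants with a notified SAE** = 86 × (1 − exp(−h × window)), where h = −ln(1 − risk) / 182.6

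At 10%, h = 0.1054 / 182.6 = 0.000577 per day. Arm 1: 86 × (1 − exp(−0.0173)) = 1.5. Arm 2: 86 × (1 − exp(−0.0700)) = 5.8 to 86 × (1 − exp(−0.0876)) = 7.2.

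| Assumed six-month risk | Arm 1 (30 days) | Arm 2 (121 to 152 days) | Either arm, full six months |
| --- | --- | --- | --- |
| 5% | 0.7 | 2.9 to 3.6 | 4.3 |
| 10% | 1.5 | 5.8 to 7.2 | 8.6 |
| 20% | 3.1 | 11.9 to 14.6 | 17.2 |

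The ratio stays at about 4 to 5 across the three risks. It falls when Arm 2 participants stop early: someone whose last treatment is at one month has a window of 30.4 + 30 = 60.4 days, about twice that of Arm 1.

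**Scheduled AE checks after randomisation.** Arm 1 has 3 follow-ups, plus the advice session if it counts, so at most 4. Arm 2 has 3 follow-ups plus up to 15 sessions, so up to 18. If follow-up is remote and section 10.2 covers face-to-face visits only, the maxima are 1 and 15.

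**The case against.** A reader might infer that Arm 1 is observed for only 30 days, that all AE assessment depends on treatment, and that safety therefore cannot be compared. The protocol does not support these readings. Both arms are followed to six months, and AEs are assessed at their face-to-face follow-up visits. The opening of section 10.4 and its Seriousness paragraph require prompt notification with no end date. Related events are notified until trial closure, so the 30-day limit bears on SAEs judged unrelated or unlikely to be related. Events in the first 30 days, or from the common visits, could still be compared. Safety is not a listed outcome (section 5.14), and section 5.18 plans no between-arm safety comparison.

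The two problems also cannot be added together. On the literal IMP reading Arm 1 has no AEs, so there is no ratio to calculate. The ratio exists only if the definition is taken to cover everyone randomised. It also assumes completed treatment, although sessions are a maximum, drugs are optional and 30% attrition is planned. The remote follow-up point is an ambiguity, since the checklist in section 10.2 is not limited to face-to-face contact, and operational detail is left to an SOP that is not shown. Closer surveillance of the arm receiving drugs is a reasoned choice, which section 10.2 explains.

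All of that stands, but it does not settle the matter. The open-ended and time-limited notification rules sit in the same section, and sites could follow either. The extension to trial closure does little for Arm 1, because Table 2 defines a reaction as a response to an IMP. Extra surveillance in Arm 2 is compatible with a common minimum in both arms.

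**Conclusion.** The point holds as a fault in the data-collection rules. As written, the SAE notification window depends on treatment: about 30 days in Arm 1 and up to about four to five months for Arm 2 participants who complete treatment. The AE definition contradicts other sections, and Arm 2 has up to 15 additional AE checks. Crude SAE and AE counts by arm should therefore not be read against each other in descriptive tables or by the DMEC.

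The contrast of 1.5 against 5.8 to 7.2 participants is an upper-end illustration. It rests on an assumed equal risk of 10% at a constant rate, full completion in Arm 2, and the time-limited rule being followed. If sites instead notify every SAE to six months, as the open-ended wording allows, the expected counts are equal. The defect is that the protocol does not say which rule governs.

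**What to change.** - Define an AE in Table 2 as any untoward medical occurrence in a randomised participant, and keep the IMP wording for adverse reactions.
- Notify SAEs in both arms from randomisation to the six-month follow-up, keeping the 30-day rule as an addition for anyone treated later than that.
- Reconcile the opening and Seriousness paragraphs of section 10.4 with its Notification paragraph and with section 10.6, so that one end date applies throughout.
- State in section 10.2 that the AE checklist is used at the one-, three- and six-month follow-ups in both arms, face-to-face or remote.
- Base by-arm safety tables on these common assessments, and report AEs elicited at Arm 2 sessions separately.

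The cost is protocol and SOP wording, a few minutes at contacts that already take place, and a few more SAE forms. At the assumed 10% risk, the extra forms would come from about 8.6 − 1.5 = 7 participants in Arm 1 and 1.4 to 2.8 in Arm 2.

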### Notification procedure

1. The SAE/SUSAR Form must be completed by the site clinician (who is responsible for the participant’s care), with due care being paid to the grading, causality and expectedness of the event as outlined above. In the absence of the responsible clinician, the form should be completed and signed by a suitably qualified member of the mental health care team or the trial researcher and sent to the country office as appropriate. The responsible clinician should subsequently check the SAE/SUSAR Form; make changes as appropriate, sign and then re-send to the respective country coordinating centre as soon as possible. The initial report must be followed by detailed, written reports as appropriate.

The minimum criteria required for reporting an SAE are the study ID and age, name of clinician reporting, the event, and why it is considered serious.

1. The SAE/SUSAR Form must be sent as a scanned copy by email to the respective country coordinating centre:

| **SAE REPORTING**  Within 24 hours of becoming aware of an SAE, please fax or email a completed SAE form to the respective country office on:  India: Fax (To Be Advised), email: (To Be Advised)  Pakistan: Fax (To Be Advised), email: (To Be Advised) |
| --- |

1. Follow-up: participants must be followed up until clinical recovery is complete (including laboratory results returning to normal or baseline if relevant), or until the event has stabilised. Follow-up should continue after completion of protocol treatment if necessary. A further SAE/SUSAR Form, by indicating as ‘Follow-up report’ should be completed and emailed to the country coordinating centre as information becomes available. Extra, annotated information and/or copies of test results may be provided separately. The participant must be identified by study ID, age and initials only. The participant’s name should not be used on any correspondence and should be deleted from any test results.
2. Staff should follow their institution’s procedure for local notification (for e.g. to drug regulatory and Research Ethics Committees (REC)/ Institutional Review Boards (IRB)) requirements.

### Country PI/ lead responsibilities

Medically-qualified staff at the country coordinating centre (the country trial manger or lead) will review all SAE reports received. The events will be coded using the Medical Dictionary for Regulatory Activities ([MedDRA](http://www.meddra.org/)). The causality assessment given by the mental health care team at the mental health facility cannot be overruled; in the case of disagreement, both opinions will be provided in any subsequent reports.

The country leads are responsible for reporting the SAEs to the competent authorities (drug regulatory authorities and REC/IRB) in their respective countries and to the University of York research team in the UK. Fatal and life-threatening SUSARs must be reported to the competent authorities (drug regulatory authorities and REC/IRB) within 7 days of the country coordinating centre being notified of the event and follow-up information within a further 8 days; other SUSARs must be reported within 15 days.

The University of York research team should be notified of all SAEs **within 24 hours** of the site mental health care team’s becoming aware of the event. The country leads should notify the University of York research team of all SAEs occurring from the time of randomisation until 30 days after the last protocol treatment administration using the SAE/SUSAR Form. SARs and SUSARs must be notified to the University of York research team until trial closure.

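### When site and country lead disagree on causality, the protocol bars overruling the site and does not say whose rating classifies the event, so a SUSAR suspected only centrally may miss the 7- or 15-day report

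*Protocol*

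**What the plan says.** Four rules in section 10 of the protocol bear on this point.

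- **Who rates causality** (10.4, Trial site assessment, Causality): "The country leads or mental health care team must assess the causality of all serious events or reactions in relation to the trial therapy".
- **How the rating classifies the event** (same paragraph, and Table 3): "If the causality assessment is unrelated or unlikely to be related, the event is classified as an SAE". By contrast, "If the causality is assessed as possible, probable or definitely related, then the event is classified as an SAR". Table 3 labels the unrelated and unlikely categories as unrelated SAEs.
- **When expectedness is assessed** (10.4, Expectedness, below Table 3): "If there is at least a possible involvement of the trial treatment, the country lead or mental health care team must assess the expectedness". Then: "If a SAR is assessed as being unexpected, it becomes a SUSAR".
- **Central review** (10.6, Country PI/ lead responsibilities): medically qualified country staff review every SAE report received. "The causality assessment given by the mental health care team at the mental health facility cannot be overruled"; the sentence goes on, "in the case of disagreement, both opinions will be provided in any subsequent reports".

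Section 10.6 sets deadlines to the competent authorities for SUSARs only. Fatal or life-threatening ones are due within 7 days of the country centre being notified, with follow-up information in a further 8 days. Other SUSARs are due within 15 days. Country leads must also report SAEs to the authorities, but no time limit is given for SAEs that are not SUSARs.

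**The concern.** A rule that protects the site's rating has different consequences in its two directions. If the site suspects the drug and the centre does not, the rule keeps the suspicion alive, which is the cautious result. If the centre suspects the drug and the site does not, the same words can keep the lower rating in place. The text draws no distinction between the two.

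What is at stake is the route and timing of the report. SUSAR status is reached only through SAR status, and the dated reports to regulators and ethics committees attach only to SUSARs. The sponsor's duty in section 10.7 to check that reporting has been done likewise names SUSARs and other SARs.

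Disagreement at this boundary is plausible. In Table 3 the descriptions of both unlikely and possible refer to the participant's clinical condition and to other concomitant treatment, so the step between them is a matter of judgement. Participants have severe mental illness, and section 10.1 lists mood changes and sleeplessness among the side effects of bupropion. Two qualified assessors could reasonably attribute a serious psychiatric event differently.

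**Working it through.** No arithmetic applies. The check is to trace an event through the written rules for each pair of ratings, under two readings:

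- **Reading A:** the site's rating, which may not be overruled, sets the class.
- **Reading B:** the country lead's own rating also counts, because 10.4 names the country lead as a permitted assessor.

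| Site rating | Country lead rating | Reading A | Reading B |
| --- | --- | --- | --- |
| Unlikely | Unlikely | Unrelated SAE | Unrelated SAE |
| Possible | Possible | SAR; SUSAR if unexpected | SAR; SUSAR if unexpected |
| Possible | Unlikely | SAR; SUSAR if unexpected | SAR, since the site's rating still stands |
| Unlikely | Possible | Unrelated SAE; no SUSAR deadline | SAR; SUSAR if unexpected, 7- or 15-day deadline |

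Only the last row separates the readings. Its steps are as follows.

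1. The 10.4 Causality paragraph classifies on a single causality assessment and does not say which one if there are two.
2. The Expectedness paragraph is triggered by at least possible involvement, again without saying in whose judgement. It allows either party to act: "the country lead or mental health care team must assess the expectedness of the event".
3. Section 10.6 forbids overruling the site. The only consequence it gives to disagreement is that both opinions are reported. It does not say that the class changes.
4. If the event is not a SAR, it cannot become a SUSAR, and neither deadline applies.

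Reading A is the more natural. The causality and expectedness rules stand under a heading about assessment at the trial site. Section 10.5 has the site clinician complete the SAE/SUSAR form, including causality and expectedness. Section 10.6 then protects that assessment. Reading B remains open because of the word *or* in 10.4.

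Some things hold for the last-row event under both readings, provided it falls within the SAE notification window. It goes to the country lead or trial manager within 24 hours (10.4, 10.5) and to the York team within 24 hours of the site becoming aware of it (10.6). It is reviewed centrally. It is reportable to the authorities as an SAE, with both opinions in subsequent reports. The difference between the readings is therefore a dated report to the authorities under B and an undated one under A.

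**The case against.** The strongest reply is that this is an ambiguity and not a stated failure. Section 10.4 gives the country lead a role in both causality and expectedness, so a lead who judges involvement possible can proceed to expectedness and open the SUSAR route. The lead's opinion is not suppressed, because it must accompany later reports. York, acting as sponsor, hears of the event within a day. Section 10.7 commits York to keeping country leads informed of safety issues, and urgent safety measures may be taken immediately whatever the classification. Operational detail is also assigned to an adverse event reporting SOP, which is not shown.

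Much of this stands, and it rules out several stronger conclusions that a reader might draw:

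- *That the site's rating alone decides SAE versus SAR.* The text does not say so, and 10.4 names the country lead as an alternative assessor.
- *That the event would next be reported only in the annual safety report.* The 24-hour notifications and the duty to report SAEs to the authorities contradict this.
- *That there is no second opinion.* Section 10.5 puts the site clinician first, and 10.6 has country staff review every SAE report.
- *That late events drop from central view because of this rule.* The 30-day limit on SAE notification in 10.4 and 10.6 is a separate matter, which the wording on overruling neither causes nor cures. The opening of 10.4 (Trial site responsibilities) also states a 24-hour SAE notification with no 30-day limit.

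The reply does not remove the core. Reporting both opinions governs what a report contains, not when it is due. An SOP can supply procedure, but it would sit awkwardly against a protocol sentence that forbids overruling. And if both readings are open, two countries could give the same event different deadlines.

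**Conclusion.** The point holds as a reporting rule that can block the more cautious classification, in sections that do not settle whose rating governs. The affected case is narrow: a serious, unexpected event that the site rates unrelated or unlikely and the country lead rates possible or higher. For that case the report to the authorities may change from one due within 7 or 15 days to one with no stated deadline.

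This rests on taking the site's rating as the one that classifies. That is the natural reading of 10.4 to 10.6 together, but not the only one. The protocol gives no SAE rate and no rate of disagreement between assessors, so the number of such events cannot be estimated from it. The target of 172 participants and the descriptive analysis do not depend on the answer. The change should be made because it concerns participant safety reporting and costs little.

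**What to change.** Reconcile the Causality and Expectedness paragraphs of 10.4 with 10.6:

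- In 10.6, replace *cannot be overruled* with *cannot be downgraded*.
- Add: *If either the site team or the country lead rates the event as possible, probable or definite, it is handled as a SAR, expectedness is assessed, and the SUSAR deadlines in this section apply; both opinions are reported.*
- In 10.4, refer to that rule at the points where the causality rating sets the class and where it triggers the expectedness assessment. Carry the same wording into the SOP.

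The cost is a short amendment to three places and the SOP, and perhaps a few extra expedited reports of events that prove unrelated. No data collection, sample size or analysis changes.
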